#### Unblinding

Where required for medical or safety reasons a trial break code can be obtained from a nominated member of the research team who will remain blinded to patient allocation. Information on the indication and outcome of the unblinding will be forwarded to the Trial Steering Committee (TSC) and included in the final trial report. While Suspected Unexpected Serious Adverse Reaction (SUSAR) reports will include the treatment allocation, this information will not be available to the trial team and blinding will be maintained.

### Outcomes

#### Primary outcome

The primary outcomes for this study are based on determining the feasibility of conducting an RCT of octreotide versus placebo infusion during liver transplantation. The feasibility will be assessed by:

Recruitment ratio (percentage of eligible patients undergoing transplantation who provide consent, target: ≥30%).Percentage of eligible patients who receive the study drug infusion in a blinded manner (target: ≥80% of patients).Incidence of drug-related serious unexpected adverse events (target: ≤20%).Completion of follow-up data collection (target: ≥90% patients).Patient refusal to enrol in study on admission for transplantation (target: ≤15%).Clinician refusal for inclusion or randomisation following patient recruitment (target: ≤15%).

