### Patient identification and recruitment

Participant screening and registration will be undertaken locally at each study site. Overall trial flow is outlined in online supplemental appendix 1.

10.1136/bmjopen-2021-055864.supp1Supplementary data

Patients will be identified and recruited in two ways, depending on whether they are undergoing assessment for suitability for liver transplantation or have already been accepted onto the waiting list for transplantation. Screening will be performed by the clinical team, as will primary contact regarding engagement with research, prior to research team contact.

i. Patients undergoing assessment for liver transplantation will be sent the patient information sheet (PIS) for this study. Patients that meet the inclusion criteria will be approached during their in-patient assessment process to explain the study and for preliminary informed consent.

ii. Patients already listed for liver transplantation who meet the inclusion criteria will be sent the PIS. These patients will be contacted by phone, the study and PIS explained, and preliminary informed consent taken.

Due to the waiting time for transplant and the fixed duration of this study many patients who would be willing to enter the study will not be able to participate because a donor organ does not become available. Both groups of patients will therefore have their consent confirmed on the day of admission for surgery at which point, once the transplant surgery has been confirmed, the patient will be considered to be enrolled.

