### Randomisation

Consented patients who proceed to transplantation will be randomised. Remote-site computerised random allocation will be performed with a centrally generated code (www.sealedenvelope.com) that will correlate with a coded syringe held in the secure study drug storage facility at each study centre. Patients will be stratified within the randomisation process by source of liver graft (brain death, DBD, or cardiac death donor, DCD) to ensure that patients are balanced for these factors across the two treatment groups. Patients will be randomly allocated to either the octreotide or placebo study groups in a 2:1 ratio. The randomisation list will be held centrally at a dedicated and independent off-site facility that will be contactable 24 hours a day.

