#### Recruitment rate

Over 275 patients per year will be eligible for study inclusion across the two study sites. With a 10 month recruitment period, this requires a 13% recruitment rate. A recent interventional trial in liver transplantation at the RFH achieved a 53% recruitment rate.^32^ Staff involvement and recruitment strategies will be similar in this study indicating this is a deliverable recruitment target.

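### The ≥80% blinded-delivery target is set on eligible patients, so as worded it is capped by the consent rate and can fail even when delivery is perfect

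*Protocol article*

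**What the plan says.** The Primary outcome section of the protocol article lists six feasibility criteria with numerical targets. Two adjacent ones matter here:

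- The recruitment ratio, a percentage, is defined as "percentage of eligible patients undergoing transplantation who provide consent, target: ≥30".
- Blinded delivery is defined as "Percentage of eligible patients who receive the study drug infusion in a blinded manner (target: ≥80% of patients".

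Two more, also percentages, deal with losses around admission: "Patient refusal to enrol in study on admission for transplantation (target: ≤15" and "Clinician refusal for inclusion or randomisation following patient recruitment (target: ≤15".

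Other sections fix who can reach the infusion. Under Patient identification and recruitment, consent is confirmed on the day of admission and, "once the transplant surgery has been confirmed, the patient will be considered to be enrolled". Under Randomisation, "Consented patients who proceed to transplantation will be randomised".

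The Recruitment rate section shows how the article uses the word *eligible*: "Over 275 patients per year will be eligible for study inclusion across the two study sites". It then applies a recruitment rate to that pool and cites a precedent: "A recent interventional trial in liver transplantation at the RFH achieved a 53% recruitment rate". Having consented is not among the inclusion criteria; the exclusion criteria remove only people who lack capacity to consent.

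**The concern.** Wherever the article counts eligible patients, it means people who may or may not go on to consent. Read that way, the delivery criterion has everyone who could have been asked in its denominator and only those who agreed and were treated in its numerator. It then mostly re-measures consent, which the first criterion already covers, and at a far higher threshold (80% against 30%).

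The trial could meet its recruitment target, infuse every randomised patient blinded, and still have to report a missed primary feasibility target. What a later trial needs to learn from this criterion is whether syringe supply, storage, coding and blinding work once a patient is in the study. The stated denominator would hide that.

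**Working it through.** **Plan's own figure.** The article gives no calculation for the 80% target. Its one precision statement, in Sample size, is about ±10 points for the consent rate with 100 approached. It reproduces: 1.96 × √(0.5 × 0.5/100) = 9.8 points, and 1.96 × √(0.3 × 0.7/100) = 9.0 points. It concerns consent and does not bear on the delivery denominator.

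**Inputs.** Recruitment target 30% and delivery target 80% (Primary outcome); 30 patients (Sample size); only consented patients randomised (Randomisation); cited precedent 53% (Recruitment rate).

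**Step 1: the ceiling.** Let E be the number eligible, C the number consenting and I the number infused blinded. Infused patients are a subset of consenting patients, so I ≤ C and I/E ≤ C/E. The delivery percentage cannot exceed the consent rate. The delivery criterion omits the recruitment ratio's restriction to patients undergoing transplantation. Taken literally, that leaves E the same or makes it larger, so the ceiling stays the same or falls.

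**Step 2: the ceiling with perfect delivery (I = C = 30).**

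| Consent rate | Eligible patients counted | Highest possible delivery | Recruitment ≥30% | Delivery ≥80% |
|---|---|---|---|---|
| 30% | 30/0.30 = 100 | 30% | met | missed |
| 53% | 30/0.53 = 56.6 | 53% | met | missed |
| 79% | 38 | 30/38 = 78.9% | met | missed |
| 81% | 37 | 30/37 = 81.1% | met | met |

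The break point is 30/0.80 = 37.5: with 30 infused, at most 37 eligible patients could be counted.

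**Step 3: imperfect delivery.** If 90% of consenting patients are infused blinded, consent would have to reach 0.80/0.90 = 88.9%.

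**Step 4: enrolled patients as denominator.** If 30 are enrolled, 80% is 24 of 30, with a Clopper-Pearson 95% CI of 61.4% to 92.3%. If all 30 are infused blinded the result is 30/30 = 100% (88.4% to 100%), whatever the consent rate.

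**The case against.** The strongest reply is that this is a loose noun and not a flawed design. The abstract lists correct delivery of the blinded treatment separately from the recruitment ratio. The target in the delivery line refers simply to patients, as does the follow-up target, which can only sensibly mean trial participants. A sensible author of the analysis plan would not choose the one reading that makes the criterion repeat recruitment. This is probably right about intent. It does not change what is written: the article states a denominator for a primary outcome and nowhere redefines it. An analysis plan using another denominator would depart from that statement. The plan need only be approved before analysis, and treatment blinding does not hide consent and delivery counts, so the choice is better fixed early.

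A second reply is that the consequence is limited. The article attaches no progression rule or statistical stopping rule to these targets and plans no formal tests. Anyone given the counts could recompute the percentage. That stands, and it limits the seriousness of the point.

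Two stronger readings are tempting but not supported:

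- **A ceiling of 13%.** A reader might take this from the Recruitment rate section. That figure is the minimum accrual needed to reach 30 patients in 10 months (30/(275 × 10/12) = 13.1%). It is not a forecast of consent, and at that rate the recruitment target is missed too.
- **A conflict with the two 15% refusal limits.** A reader might multiply 0.85 × 0.85 = 72% and conclude that these limits contradict the 80% target. This needs both refusals at their limits, in sequence, with refusers kept in the delivery denominator. Patients who refuse on admission are never enrolled, and separate criteria need not all pass when each is at its limit.

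**Conclusion.** The point holds for the criterion as worded. The delivery percentage is capped by the consent rate, and every consent rate from 30% to below 80% gives a met recruitment target and a missed delivery target, even with perfect blinded delivery. The cap is 30% at the recruitment target.

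The 53% cap assumes that the precedent is a consent rate among eligible patients; the article does not give its denominator. The general result assumes only that *eligible* keeps the pre-consent meaning it has in the recruitment ratio and the Recruitment rate section.

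A reader might go further and infer that the trial is bound to be declared infeasible. The documents do not support that: the probable intent is attainable, and no decision rule hangs on this target alone. The fault is a misdefined primary feasibility measure. It should be corrected, but it does not endanger patients or invalidate the trial.

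**What to change.** Change the denominator from eligible to enrolled patients, for example: *share of enrolled patients (consent confirmed on admission, surgery confirmed) given the study infusion with blinding intact; target at least 80%, which is 24 of 30 if 30 are enrolled*. Report the percentage of randomised patients alongside.

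Enrolled is better than randomised as the main denominator. Someone who confirms consent but is not randomised for a logistical reason, such as no in-date syringe on site, counts as a recruitment success and is nobody's refusal. With randomised patients alone, no criterion would show that loss. Consent and refusal losses before enrolment stay with the recruitment and patient-refusal criteria.

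The cost is one word in one line plus one extra reported percentage. Enrolment is already a defined event, so no new data are needed. There is some overlap: a clinician refusal after enrolment would count in both the clinician-refusal and the delivery criteria. If such refusals reached 15% of enrolled patients, 0.80/0.85 = 94.1% of the rest would have to be infused blinded. The randomised percentage shows whether a shortfall arose before or after randomisation. The Protocol amendments section already provides for flagging changes from the article in the results paper.

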## Abstract

**Introduction:**

Liver transplantation is a complex operation that can provide significant improvements in quality of life and survival to the recipients. However, serious complications are common and include major haemorrhage, hypotension and renal failure. Blood transfusion and the development of acute kidney injury lead to both short-term and long-term poor patient outcomes, including an increased risk of death, graft failure, length of stay and reduced quality of life. Octreotide may reduce the incidence of renal dysfunction, perioperative haemorrhage and enhance intraoperative blood pressure. However, octreotide does have risks, including resistant bradycardia, hyperglycaemia and hypoglycaemia and QT prolongation. Hence, a randomised controlled trial of octreotide during liver transplantation is needed to determine the cost-efficacy and safety of its use; this study represents a feasibility study prior to this trial.

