#### Risks

Octreotide is not currently licensed for use in liver transplantation. Common risks of octreotide include changes in blood sugar levels, heart rate and rhythm. The side effect profile of octreotide during liver transplantation is unknown. The studies to date did not compare safety or adverse events between the octreotide and placebo arms,^15^ have not been fully published^25^ or did not assess adverse events.^24^

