#### Study drug

Octreotide is licensed in the UK and is being used outside of its marketed authorisation for the purpose of this trial. The Summary of Product Characteristics will be used as a safety reference and the dose will not exceed the maximum dose of 1.5 mg/day. A suitable marketed product will be sourced by the RFH Pharmacy Manufacturing Unit that allows 7 days stability after reconstitution. The study drug will be prepared and released by a Qualified Person for use in the study by the holder of a Manufacturing and Import Authorisation (Investigational Medicinal Products) licence.

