#### Secondary outcomes

A number of secondary outcome measures will be collected to help shape future trials in terms of assessing potential primary outcome measures and monitoring safety end points.

Intraoperative cell salvage volume (as a proxy for blood loss).Intraoperative urine output during each surgical phase.Mean arterial blood pressure during each surgical phase.Requirement for and mean vasopressor and/or inotrope infusion rate during each surgical phase.Volume or mass of de novo packed red blood cells and other clotting products during surgery and on the ICU (within first 24 hours, 72 hours and 1 week).Incidence of AKI as defined by the Acute Kidney Injury Network stage 1 criteria (a 50% increase in serum creatinine from baseline or less than 0.5 mL/kg/hours urine output for 6–12 hours post transplant) within 24 hours, 72 hours, 1 week.Incidence of postoperative RRT at 24 hours, 72 hours, 1 and 2 weeks postoperatively.Incidence of new or worsened CKD at 30 and 90 days.Mortality, early allograft dysfunction, graft loss and liver graft function at 30 and 90 days.Patient recorded outcome measures (PROM) preoperatively and at 90 days postoperatively;Liver Disease Quality of Life questionnaire.^28^EuroQOL-5D-5L questionnaire.^29^

Major safety outcomes will include:

Unexpected or resistant bradycardia,.Abnormal QTc interval (460 ms in men, 470 ms in women) or associated ventricular arrhythmia or Torsades de Pointes.Unexpected or resistant hypoglycaemia (blood sugar <4 mmol/L).Potential allergic or anaphylactic reaction to any medication.Any report of an abnormal response to codeine or morphine.Development of venous or arterial thrombosis.Cardiac event including acute coronary syndrome, new heart failure, arrhythmia or resuscitated cardiac arrest.

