### Sample size

Thirty patients will be recruited from two sites, with 20 in the study drug (octreotide) arm and 10 in the placebo. This sample will allow us to demonstrate the feasibility of conducting a full-scale randomised trial. This study is not powered to detect differences in treatment effect but will obtain estimates of an effect and its variance.^30^ This sample size will allow us to estimate patient consent rate with a 95% CI of ± 10% (based on 100 participants approached). The secondary outcome data will provide the required information for a sample size calculation for the primary end point of a subsequent trial.^31^ Survival to discharge is above 96% for both study sites and hence it is likely that the ninety day follow data collection will be achieved for the majority of patients.

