### Statistical methods

A statistical analysis plan will be approved by the TSC, prior to data analysis.

The following variables will be used to assess baseline comparability of the randomised groups:

Study centre at which transplant performed.Age.Sex.The model for end-stage liver disease score.^33^The UK end-stage liver disease score.^34^Aetiology of liver disease.The UK donor risk index.^35^Organ graft undergoing normothermic machine perfusion.Presence of portal hypertension.Severity of preoperative renal dysfunction (estimated glomerular filtration rate).American Society of Anesthesiologists score.Pr-operative haemoglobin level.EuroQol-5D-5L questionnaire scores.Liver disease Quality of Life questionnaire score.

Patients will be analysed according to the groups to which there were randomised.

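### The only safety criterion with a target counts unexpected drug-related serious events alone, so serious cases of octreotide's named risks need not count towards it

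*Protocol article*

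**What the plan says.** All places are in the Protocol article.

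- **Outcomes, Primary outcome.** Six feasibility measures carry targets. The safety one is "Incidence of drug-related serious unexpected adverse events (target: ≤20"%). It defines neither unexpected nor the arm, denominator or time window. A neighbouring item does say whom it counts: "Completion of follow-up data collection (target: ≥90% patients").
- **Study drug.** "The Summary of Product Characteristics will be used as a safety reference".
- **Abstract, Introduction.** "octreotide does have risks, including resistant bradycardia, hyperglycaemia and hypoglycaemia and QT prolongation".
- **Risks.** "Common risks of octreotide include changes in blood sugar levels, heart rate and rhythm". The same section says that the side effect profile in liver transplantation is not known.
- **Secondary outcomes.** A list of major safety outcomes, without targets, covers bradycardia, QTc and ventricular arrhythmia, cardiac events and "Unexpected or resistant hypoglycaemia (blood sugar <4 mmol/L").
- **Table 1.** Adverse events attributed to the study infusion are a key secondary outcome, with no filter for seriousness or expectedness.
- **Adverse events.** All SAEs to 90 days from enrolment are recorded, and they are to be reported to discharge, to 30 days and to 90 days.
- **Sample size.** Thirty patients, "with 20 in the study drug (octreotide) arm and 10 in the placebo".
- **Statistical methods.** "Patients will be analysed according to the groups to which there were randomised". Primary measures are given as counts and percentages with exact 95% CIs.

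**The concern.** Related, serious and unexpected together are the elements of a SUSAR, a category that the article uses under Unblinding and Adverse events for regulatory reporting. A SUSAR count shows whether something not anticipated has appeared. It does not show whether patients tolerate the drug. The harms that motivate the safety question here are the anticipated ones: heart rate, rhythm and blood sugar. A serious case of any of them, judged due to octreotide, can be classed as expected and fall outside the only safety measure that has a limit.

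The Abstract's methods paragraph describes this primary outcome simply as adverse event rates, which is wider than what the criterion measures. The results paper could therefore report the safety target as met, in support of a larger trial, when the criterion had not tested the named harms. No interim analysis and no statistical stopping rule is planned, so no other numerical safety limit stands behind it.

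**Working it through.** **1. The plan's own precision figure.** The only one is a half-width of ±10% for the consent rate with 100 approached. It reproduces: 1.96 × √(0.5 × 0.5 / 100) = 0.098. It says nothing about the safety item, and no figure is given to justify the 20% limit.

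**2. What the limit allows.** With 20 octreotide patients, ≤20% means at most 0.20 × 20 = 4 affected. The exact 95% CI for 4/20 is 5.7% to 43.7%.

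**3. Effect of the expectedness filter.** Let R be the true proportion of octreotide patients with a serious drug-related event, and f the share of those patients whose event is classed as unexpected. The criterion then sees a rate of R × f, and

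P(target met) = P(X ≤ 4), with X ~ Binomial(20, R × f).

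R and f are assumptions, since the documents give neither.

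| R | f | Rate scored (R × f) | P(target met) |
|---|---|---|---|
| 0.30 | 1 (all count) | 0.300 | 0.24 |
| 0.30 | 0.5 | 0.150 | 0.83 |
| 0.30 | 0.25 | 0.075 | 0.99 |
| 0.30 | 0 | 0 | 1.00 |
| 0.50 | 1 (all count) | 0.500 | 0.006 |
| 0.50 | 0.5 | 0.250 | 0.42 |
| 0.50 | 0.25 | 0.125 | 0.91 |
| 0.50 | 0 | 0 | 1.00 |

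**4. The same thing in counts.** Suppose 6 of 20 octreotide patients had such an event: 30%, exact 95% CI 11.9% to 54.3%. If all six were classed as expected, the criterion would read 0/20, CI 0% to 16.8%. Even the upper confidence limit would then lie below the target.

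**5. Denominator, a separate and weaker point.** Here all events are taken to count, so this result must not be added to step 3. Pooled over 30 patients, ≤20% allows 0.20 × 30 = 6. Six affected octreotide patients are 6/30 = 20% (met) but 6/20 = 30% (not met). At R = 0.30 the chance of meeting the target is 0.24 with the octreotide arm alone. When pooled it depends on q, the proportion of placebo patients judged under blinding to have a related event:

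| q | P(target met), pooled |
|---|---|
| 0 | 0.61 |
| 0.05 | 0.51 |
| 0.10 | 0.43 |
| 0.20 | 0.27 |

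**The case against.** The strongest reply is that nothing is hidden. Table 1, the major safety list and the SAE reporting all capture these events, and secondary outcomes are compared between groups with 95% CIs. The Trial Management Group reviews SAEs, and the TSC, which also serves as data monitoring committee, can recommend stopping. The article does not say that progression to a larger trial rests on this one item. In a population with a 70% complication rate, judging relatedness under blinding is noisy, and an expectedness filter adds some specificity. All of this stands. It means that the events are lost from the targeted criterion and not from the trial. It does not give the wider count a limit.

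Three stronger readings are tempting, and the documents do not support them.

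- **The named risks would score zero.** Unexpected is not defined for this item. The Summary of Product Characteristics is called a safety reference, but its contents are not shown. The secondary list treats some bradycardia and hypoglycaemia as possibly unexpected. The f = 0 rows above are therefore an extreme and not a forecast.
- **Placebo patients will dilute the rate.** No sentence pools the arms for this item. Analysis by randomised group points the other way, the statistical analysis plan (not shown) may settle it, and blinded attribution of placebo events narrows the gap.
- **Hyperglycaemia is overlooked.** The Abstract names it and the major safety list does not. However, drug-related cases would fall under the Table 1 outcome, so this is at most minor.

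An analysis plan that fixed the denominator would still not remove the word unexpected from the primary outcome, because the protocol itself sets that restriction.

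**Conclusion.** The point holds in this form: the one safety criterion with a target is in effect a SUSAR rate, so serious drug-related events of the kinds the article calls known risks need not count, and the target can be met while they are frequent. At an assumed true rate of 30% in 20 octreotide patients, the chance of a pass rises from 0.24 with all events counted to 0.83 if half are unexpected and 1.00 if none are. The sizes rest on the assumed rate, on the assumed share classed as unexpected and on all 20 patients receiving octreotide. The direction does not depend on them, since any exclusion of expected events can only lower the rate scored. The missing denominator is a secondary ambiguity. A reader should not conclude that the trial ignores these harms or that a false claim of tolerability must follow, because the events are reported elsewhere without a limit.

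**What to change.** Redefine the primary safety criterion as the number of patients who received octreotide and had at least one serious adverse event judged drug-related, expected or not, divided by all patients who received octreotide. State the window, for example the 90 days for which SAEs are already recorded. Show the placebo figure beside it, and report unexpected events as a separate count. Have the TSC confirm, before unblinding, whether 20% is still the right limit for this wider count. Naming octreotide recipients as the denominator also rules out the pooled reading in step 5.

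The cost is a change of wording in the protocol and analysis plan plus one TSC decision. No new data collection is needed. The statistician, who sees only treatments A and B, can calculate the figure for both coded groups and identify the octreotide group at unblinding. The downside is that the reported rate may look less favourable, and the 20% limit has to be reconsidered and not simply carried over.
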